#### Cerebral blood flow analysis

The task-related relative changes (Δμmol) in oxy-Hb and deoxy-Hb will be estimated using MATLAB-based software NIRS Brain AnalyzIR Toolbox (https://github.com/huppertt/nirs-toolbox [67]). Oxy-Hb will be the predominant cerebral blood flow outcome as it has previously been reported to be the most sensitive indicator of neural activation [68]. FNIRS probe registration will be individualised to account for anatomical differences and probe placement, by using head circumference, nasion-inion, and pre-auricular distances from each participant. Quality check of each signal will be initially performed, including checking the relative coefficient of variation (CV%) for each channel. A CV% less than 15% will indicate good signal quality. Poor signal quality will be dealt with in the statistical analysis. Raw voltage will then be converted to optical density and subsequently to haemoglobin concentrations based on the modified Beer-Lambert law [52]. Data will be processed and analysed in a similar manner outlined in Heiland et al. [52]. Minimal manipulation will be performed on the signals as suggested by Santosa et al. [67]. First level statistics will involve estimating the fNIRS parameters during the 1-, 2-, and 3-back tasks (each 35 sec duration) relative to the baseline (20 sec rest). Brain activation will be predicted using a general linear model (GLM) with a canonical design matrix and an autoregressive pre-whitening approach with iteratively reweighted least squares (AR-IRLS) for each source-detector pair. The AR-IRLS approach will be used because it reduces the false-discovery rate [69]. Short-separation regressors will be used to control for type I errors caused by systemic physiology and motion artefacts. The GLM will yield regression coefficients (betas) for each channel in each n-back task and condition that will be used in the second-level analyses (group-level analysis). This will entail the coefficients of Δoxy- and Δdeoxy-Hb each being averaged across the prefrontal region, and separately by left and right prefrontal hemispheres for each n-back task and condition. A False Discovery Rate (FDR) correction using a Benjamini-Hochberg procedure will be used to correct for multiple comparisons (*q-value* = FDR-adjusted *p ≤ 0*.*05*). Linear mixed effect models will be employed with Δoxy- and Δdeoxy-Hb as dependent variables, with condition and time as fixed effects and subject as a random effect to assess within and between condition differences in CBF parameters comparing the n-back tasks. Linear mixed effects models with maximum likelihood estimation will help to deal with potential missing data. Number of missing data will also be reported and checked for missing data mechanisms. Additional, linear mixed models will be performed to assess intervention effects including time and condition as interaction terms.

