### Sample size

To the best of our knowledge no studies have investigated the acute effects of nitrate consumption on cognitive function nor vascular health in adolescents. Therefore, an adult population was used to calculate effect sizes for the effect of nitrate on these outcomes, however, the adolescent population was used to calculate effect sizes for the effect of breakfast on working memory and psychological outcomes. Arterial stiffness and CBF mechanistic outcomes have less variance than cognitive performance and psychological factors, thus the sample size was calculated from effect sizes of working memory performance and psychological outcomes. Effect sizes were calculated on G*Power software (Franz Faul, Universität Kiel, Germany, v 3.1.9.2) using differences between two dependent means and standard deviations. The sample size was calculated: using α = 0.05, β = 0.8, correlation = 0.5 and assuming a two-tailed test. The effect size based on the effects of nitrate on working memory = 0.63, giving a sample size = 22. The effect size based on the effects of breakfast on psychological factors ranged from 0.67 to 0.48, giving a sample size range between 20 and 36. Our sample size will thus be the largest number found here with seven additional participants to account for 20% drop out rate, thus n = 43.

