### Statistical methods

#### Working memory, psychological factors, arterial stiffness, and nitrate/nitrite analysis

Linear mixed effect models, with an unstructured covariance structure, will be used to estimate within condition changes in working memory reaction time and accuracy, psychological factors, arterial stiffness, and nitrate/nitrite concentrations from time point 1 to time point 2 using Stata/SE 17.0 (StataCorp, LLC, Texas, USA). Additional models will be performed with condition and time interactions to assess between condition changes in mean differences in these outcomes.

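### Missing data is no reason to choose maximum likelihood over REML; with about 34–36 completers, REML with small-sample degrees of freedom is a cheap improvement

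*Protocol article*

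**What the plan says.** Two neighbouring sections of the protocol article describe the mixed models.

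- **Working memory, psychological factors, arterial stiffness, and nitrate/nitrite analysis:** here the model is set out as "Linear mixed effect models, with an unstructured covariance structure, will be used to estimate within condition changes", with the change taken "from time point 1 to time point 2 using Stata/SE 17.0". Further models add condition-by-time interactions for the between-condition comparisons. No estimator is named, and it is not said whether the unstructured covariance is that of the residuals or of the random effects.
- **Cerebral blood flow analysis:** here the estimator is named: "Linear mixed effects models with maximum likelihood estimation will help to deal with potential missing data". These models have fixed effects of condition and time and a random effect for the participant; the word unstructured does not appear.

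Neither section says whether the tests use z/chi-square or t/F reference distributions. The Sample size section fixes the scale: 36 participants plus "seven additional participants to account for 20% drop out rate, thus n = 43".

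**The concern.** The one reason given for ML is missing data. ML and REML are both likelihood methods, both keep a participant's incomplete records, and both are valid under the same missing-at-random assumption. ML therefore gains nothing on the point for which it is named. What it does differently is divide by the number of participants rather than by the degrees of freedom left after the means are estimated, so its variances are slightly too small.

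That is negligible in a large trial. With about 35 participants and six measures each (three conditions, two time points) it can be seen, above all if large-sample critical values are used as well. The between-condition conclusions, including the primary one on working memory, rest on condition-by-time terms. An understated standard error would make those tests mildly liberal and their intervals mildly too narrow. The Benjamini-Hochberg step in the CBF section would not repair this, because it takes the p-values as given.

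**Working it through.** **1. The plan's own sample size.** Inputs from the Sample size section: "using α = 0.05, β = 0.8" (the 0.8 is evidently power), "correlation = 0.5 and assuming a two-tailed test", "The effect size based on the effects of nitrate on working memory = 0.63, giving a sample size = 22", and effect sizes for psychological factors that "ranged from 0.67 to 0.48, giving a sample size range between 20 and 36". Exact power of a two-sided paired t-test:

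- d = 0.63: n = 22, power 80.4%
- d = 0.67: n = 20, power 81.1%
- d = 0.48: n = 36, power 79.96% (37 strictly)

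The stated sizes reproduce within rounding. Completers are 43 − 7 = 36 or 43 × 0.8 = 34.4, hence 34 to 36.

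**2. Adverse reading: ML, unstructured residuals, z/chi-square tests.** Assume complete data, normal errors and a separate mean for each condition and time. The ML variance is (n − 1)/n times the unbiased one.

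- *One contrast (1 df).* Rejection rate under no effect = P(|t(n−1)| > 1.96 × √((n−1)/n)). At n = 34 the cut-off is 1.96 × √(33/34) = 1.931 on 33 df.
- *Interaction (2 df).* The Wald statistic is Hotelling's T² × n/(n−1), compared with 5.991. Since T²(n−2)/(2(n−1)) follows F(2, n−2), the rate is (1 + 5.991/n)^(−(n−2)/2). At n = 34: (1 + 5.991/34)^(−16) = 7.45%.

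| n | ML, 1 df | ML, 2 df | REML, 1 df | REML, 2 df |
|---|---|---|---|---|
| 34 | 6.21% | 7.45% | 5.85% | 6.93% |
| 35 | 6.18% | 7.37% | 5.82% | 6.87% |
| 36 | 6.14% | 7.30% | 5.80% | 6.81% |
| 43 | 5.95% | 6.90% | 5.67% | 6.50% |

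All columns use z/chi-square references. Simulation of the ML case (200,000 trials per n, n = 34 to 36) gave 6.1–6.3% and 7.3–7.5%; a 2-df likelihood-ratio test gave 5.9–6.0%. The nominal 95% interval for one contrast covers about 93.8% and is about 5% narrower than the exact t interval.

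**3. Share due to ML.** At n = 34 the excess over 5% is 1.21 points (1 df) and 2.45 points (2 df). Under REML with the same references it is still 0.85 and 1.93 points. ML therefore adds 1.21 − 0.85 = 0.36 and 2.45 − 1.93 = 0.52 points; the rest comes from the large-sample reference. REML with the exact t/F reference gives 5.0% on complete data.

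**4. Milder readings.**

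- ML variances with t(n−1) critical values: 5.3% (1 df).
- Participant random intercept only, ML, z/chi-square, compound symmetry true: ML residual variance = SSE/(5n), exact reference on 5(n−1) df. This gives about 5.5% (1 df) and 5.7% (2 df), with intervals about 2% narrow. Simulation at n = 35 (20,000 trials): 5.5% and 5.7%.
- The same random-intercept model, with an assumed effect shared by the two measures of one visit: conservative, about 1.1% (1 df) and 0.6% (2 df).

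**The case against.** A reader might infer that the plan fits every model by ML with an unstructured covariance, and that its tests therefore run above 5% for every outcome. The article does not support that.

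- **The two choices are never joined.** ML is named under CBF, a secondary outcome, for models with a participant random effect. Unstructured appears in the other section, which names no estimator. The ML sentence can be read as general, but it does not say so.
- **The reference distribution is not stated.** The adverse figures need z/chi-square tests. A degrees-of-freedom method is commonly left to a statistical analysis plan, so its absence from a condensed article is not an error.
- **The direction is not certain.** For a random-intercept model the test can even be conservative, as step 4 shows.
- **The hypotheses are mostly pairwise.** That makes the 1-df figure the more relevant one; no section names a 2-df omnibus test as decisive.
- **The sample may be larger.** The abstract recruits at least 43, and mixed models keep partial records; at n = 43 the adverse figures are 5.95% and 6.9%.
- **The ML sentence is true as far as it goes.** Likelihood fitting does help with incomplete data, and the article does not claim that REML would not.

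All of this stands, and it rules out calling the plan wrong as written. What it leaves untouched is that the only stated ground for ML applies equally to REML, which has less variance bias in these models at this size.

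**Conclusion.** The point holds as a cheap improvement. ML is named with a reason that does not distinguish it from REML, at a sample size where the difference is small but not nil. Any inflation is conditional: about 6.1–6.2% for one contrast and 7.3–7.5% for the 2-df interaction if ML, unstructured residuals and large-sample tests are combined, and 5.3% to about 5.7% under the milder readings. Most of the excess in the adverse case comes from the reference distribution, not from ML, so changing the estimator alone would not be enough. The figures assume complete, balanced, normal data; missing records would make the inflation under the adverse reading somewhat larger.

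**What to change.** - Fit all mixed models, in both sections, by REML.
- Use Kenward-Roger (or Satterthwaite) degrees of freedom with t and F tests, and report the matching intervals. This is the larger part of the correction.
- Say whether the unstructured covariance applies to the residuals or to the random effects.
- Drop ML as the missing-data rationale; say instead that likelihood-based mixed models use all available records under a missing-at-random assumption.

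The cost is a change of model options and a sentence or two of text, with no new data. Intervals become slightly wider and p-values slightly larger: for one contrast in the adverse case, intervals about 5% wider.

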
## Discussion

This study will provide understanding into whether increased nitrate intake can improve working memory performance in adolescents. Furthermore, insight into changes in task-related CBF as a possible mechanism explaining the effects of nitrate on cognitive performance will be explored and if improvements will also be observed in arterial stiffness and psychological well-being. Previous studies have only investigated these acute effects in adults, resulting in mixed results [14]. This will be the first study to be performed in adolescents.

In addition, the effect of having breakfast or skipping breakfast and whether this mealtime should be promoted for adolescent’s cognitive performance, vascular, and psychological health will be investigated. Previous acute studies in adolescents have shown mixed findings on the effects of breakfast compared to no breakfast on memory, attention, and executive function [33]. Many of these studies have not reported important factors, such as how much breakfast was consumed, fasting requirements, as well as not controlling for food consumed the evening before [33]. Thus, it is important to further investigate the effect of breakfast on working memory and control for these methodological factors to provide more robust findings. It is also crucial to investigate the acute effects of breakfast on CVD-related risk factors using intervention studies. Previous research has found regular breakfast consumption to have positive benefits on CVD-related risk factors [35, 36], which is promising, however not causal. If positive acute effects of breakfast on CVD-related risk factors can be shown in this study, then this could pave the way for intervention studies of longer duration that focus on the effect of habitual breakfast consumption and risk factors related to CVD. This would provide more evidence into the relationship between regular breakfast consumption and CVD-related risk factors.

There are many strengths of this study. First is the crossover, randomised study design will provide results of high statistical power and will lower the risk of confounding errors since all participants will be their own controls. The use of modern technology in measuring task-related CBF by fNIRS with short separation channels with advanced statistical approaches, which is recommended for optimal results [70], is another strength of this study. This technology offers non-invasive quantification of cortical haemodynamic responses [71] and has a higher degree of tolerance to motion artefacts in comparison to other neuro-imaging instruments [72]. The SphygmoCor XCEL system for measuring PWV and AIx has been validated and shown to provide accurate results [73] and follows the guidelines laid out by the Artery Society Guidelines [74]. The standardisation of physical activity and diet via a diary and objectively measuring physical activity are additional advantages of this study.

Participants may not adhere to drinking beetroot juice, which is a. However, providing regular breakfast foods to be consumed with the nitrate-rich beetroot juice and providing a small glass of orange juice to wash away the taste will help to resolve this issue. Participants may also become distracted during the cognitive task, nonetheless headphones to protect from surrounding noise will be provided, tests will be conducted in a non-disruptive laboratory setting, and mind-wandering will be reduced with counting tasks. The lack of pseudo-randomisation of n-back tasks of different loads may also lead to some anticipatory effects, however, the block-design and randomised crossover nature of this study may help minimise this. In addition, maintaining an order of the task loads can help reduce confusion during the testing. Results may also be affected by the participants socialising in between tests, thus they will be continuously monitored.

This study will be informative on the acute effects of nitrate as well as breakfast on working memory, cardiovascular risk factors, and psychological well-being. Consequently, this may have important implications for school academic achievement. Furthermore, the results could influence dietary recommendations on nitrate-rich foods and breakfast consumption in this population. It is vital to investigate these effects early in life as improvements in health could translate into adulthood. This may help to reduce the risk of future cognitive impairment and cardiovascular health problems; thus, having significant implications on public health. It will also be a starting point for more research looking at the effects of breakfast and its composition (e.g. nitrate-rich) on cognitive and vascular outcomes. In turn, results can inform public health interventions and help in the development of recommendations to improve the health of adolescents.

### Trial status

This is the first version of the main study protocol. Recruitment commenced in January/February 2022, and data collection commenced in late February 2022.

## Abbreviations

CBF: cerebral blood flow
oxy-Hb: oxygenated haemoglobin
deoxy-Hb: deoxygenated haemoglobin
NO: nitric oxide
PWV: pulse wave velocity
AIx: augmentation index
fNIRS: functional near-infrared spectroscopy
PANAS: Positive and Negative Affect Scale
VAS: visual analogue scale
CVD: cardiovascular disease
